### Lost to follow up

Patients who fail to attend to their appointments will be contacted by telephone at least twice before they will be considered lost to follow up. The attrition rate and the reasons of ‘lost to follow up’ will be specifically collected during the study.

### Withdrawal criteria

Patients will withdraw from the study if the bandages cause them adverse reactions that preclude them from continuing the study or under circumstances that prevent them from keeping the assigned bandages or performing the follow-up visits.

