### Data collection

During the nursing consultation (in the health centre or at home), the individuals eligible for inclusion in the study will be informed of their eligibility and offered a chance to participate. If they accept, the patients will be checked to see if they meet all the eligibility criteria and will be requested to complete and sign the informed consent. Data collection will be performed every 14 days during the 12-week follow-up or will finish early if the ulcer has healed.

The information will be collected through clinical interviews and wound examinations, and the information will be recorded in the eCRFs. We will record those patients who decline to participate in the study (age and sex), as well as the losses, attrition and their causes. We will also record those patients who withdraw due to the withdrawal criteria.

The researchers will record the severe or unexpected adverse reactions regarding the product and will notify the principal investigator.

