### Analysis

Descriptive analysis of each variable with its corresponding 95 % confidence interval. Normality tests. Description of the profile of patients who withdraw from the study and their reasons for withdrawal.Comparison of the group at the beginning of the trial with regard to their descriptive and response variables and predictors. Bivariate statistical tests will be employed that are suitable for the variable type (qualitative or quantitative).Primary effectiveness analysis: A comparison will be performed of the incidence rates of ulcers with complete healing, using the ratio of incidence rates, with their point estimate and 95 % confidence interval. We will compare the time to complete healing using Kaplan-Meier curves for both types of treatment (log-rank test). To adjust for prognostic factors, we will perform a Cox regression model, with the time elapsed to complete healing as the dependent variable, complete healing as the event and the intervention group as the independent variable. We will include in the model those variables that can act as confounding factors or that can modify the effect.Secondary effectiveness analysis: For each secondary variable, we will apply the appropriate statistical technique based on the character of each variable (qualitative or quantitative) and to the distribution to which they fit (parametric or nonparametric).

The individuals responsible for performing the analysis will be unaware of which intervention each patient included in the study has undergone. All statistical analyses will be performed by intent-to-treat, using the conventional level of statistical significance (0.05).

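### Failure to keep the assigned bandage ends study participation, so outcomes that the promised intention-to-treat analysis needs go uncollected for treatment-related reasons

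*Protocol article*

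**What the plan says.** The Withdrawal criteria section of the Protocol article has one sentence with three routes out:

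- Bandage reactions: "Patients will withdraw from the study if the bandages cause them adverse reactions that preclude them from continuing the study".
- Inability to keep the assigned bandage, and inability to attend visits, taken together: "under circumstances that prevent them from keeping the assigned bandages or performing the follow-up visits".

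All three routes lead out of the study. The Analysis section states: "All statistical analyses will be performed by intent-to-treat, using the conventional level of statistical significance (0.05"). Its primary comparison of healing incidence is made "using the ratio of incidence rates, with their point estimate and 95 % confidence interval", followed by Kaplan-Meier curves with a log-rank test and a Cox model.

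For patients who leave, two things are planned. Data collection says "We will also record those patients who withdraw due to the withdrawal criteria", and Analysis adds "Description of the profile of patients who withdraw from the study and their reasons for withdrawal". Missed appointments have their own section (Lost to follow up), with at least two telephone contacts before a patient counts as lost. Nothing in the article provides for assessing the ulcer after a withdrawal.

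**The concern.** Intention to treat asks what happened to everyone randomised, in the arm assigned, whatever bandage they ended up wearing. A rule that ends participation because the assigned bandage was not kept removes the observations this analysis needs. Unlike ordinary loss, these gaps are made by the protocol and depend on the treatment under test.

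The arms differ in ways that could affect who leaves. The Background gives 15-20 mmHg at the ankle for crepe and light single-layer bandages and up to 40 mmHg for multilayer systems. The intervention cannot be blinded, and patients are treated by their own nurses, so the decision to leave can depend on the arm.

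If the survival analyses censor leavers, they assume that a leaver would have gone on to heal like those who stayed in the same arm. Where exit follows a bandage reaction or failure to keep the bandage on, that is doubtful. The Discussion calls the trial pragmatic, and the pragmatic effect of assigning a two-layer bandage includes the patients who cannot wear it. A later analysis plan can choose how to treat missing outcomes, but it cannot recover outcomes that were never collected.

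**Working it through.** **Passages side by side**

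| Question | What the article provides |
|---|---|
| Does not keeping the bandage end participation? | Yes (Withdrawal criteria) |
| Are all analyses by intention to treat? | Yes (Analysis) |
| Is healing assessed after such an exit? | Not provided for |
| How does a leaver count in the primary analysis? | Not stated; censoring is the default of the methods named |

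**The plan's own figures.** Inputs from Sample size: 58% healing with multilayer bandages, a 20-point difference (so 38% with crepe), alpha 0.05, power 80%. Two-sided, pooled variance, no continuity correction, mean proportion 0.48:

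n = [1.960 × √(2 × 0.48 × 0.52) + 0.842 × √(0.58 × 0.42 + 0.38 × 0.62)]² / 0.20² = 96.8, so 97 per arm. Then 97 / 0.90 = 107.8, so 108. Both reproduce, and no stated figure is in dispute.

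**How much could the rule matter?** The article gives no withdrawal rate by arm, so the following are assumptions:

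- Constant healing hazards giving 58% and 38% at day 84: h = −ln(0.42)/84 = 0.01033 (two-layer) and c = −ln(0.62)/84 = 0.00569 (crepe) per day.
- A share w of an arm has an exit time spread uniformly over days 0 to 42; those already healed by then count as healed.
- Before exit, leavers heal at their own arm's hazard. Afterwards they heal at k × c, with k from 0.25 to 1.

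Probability that a leaver is unhealed at day 84, with g the hazard before exit (h or c):

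U = exp(−84kc) × [1 − exp(−42(g − kc))] / [42(g − kc)]

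True healing in an arm = (1 − w) × p + w × (1 − U), with p = 0.58 or 0.38. Kaplan-Meier with leavers censored still returns 58% and 38%, a 20-point difference, because the hazard before exit is the same for leavers and stayers.

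*Worked case: 15% v 5% exits, k = 0.5.*

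- Two-layer: U = 0.7874 × 0.858 = 0.676; healing = 0.85 × 0.58 + 0.15 × 0.324 = 54.2%.
- Crepe: U = 0.7874 × 0.943 = 0.742; healing = 0.95 × 0.38 + 0.05 × 0.258 = 37.4%.
- All-randomised difference 16.8 points, against 20 with censoring.

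| Exits, two-layer v crepe | k = 0.25 | k = 0.5 | k = 1 | Censored |
|---|---|---|---|---|
| 10% v 5% | 17.8 | 18.1 | 18.6 | 20 |
| 15% v 5% | 16.2 | 16.8 | 17.9 | 20 |
| 20% v 5% | 14.6 | 15.5 | 17.1 | 20 |
| 5% v 10% | 20.3 | 19.9 | 19.3 | 20 |
| 5% v 15% | 21.3 | 20.6 | 19.3 | 20 |
| 5% v 20% | 22.3 | 21.2 | 19.3 | 20 |

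Entries are all-randomised differences in percentage points.

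**Counting leavers as not healed instead** (k = 0). U becomes 0.811 (two-layer) and 0.889 (crepe). At 20% v 5% the arms show 0.80 × 0.58 + 0.20 × 0.189 = 50.2% and 0.95 × 0.38 + 0.05 × 0.111 = 36.7%, a difference of 13.5 points against a true 14.6-17.1. At 5% v 20% the same rule gives 56.0% − 32.6% = 23.4 points against a true 19.3-22.3. This rule also errs, so analysis alone does not solve the problem; collecting the outcomes does.

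**The case against.** Several stronger readings are tempting, and the article does not support them.

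- *Intention to treat is impossible.* Not so. For the yes/no endpoint at 12 weeks, leavers could stay in their assigned arm and be counted as not healed. What the rule prevents is an analysis on observed outcomes for everyone randomised.
- *The trial is an on-treatment analysis under another name.* That requires leavers to be censored, and the article nowhere says so. Censoring is an inference from the methods named. How missing outcomes are handled may properly sit in an analysis plan or full protocol that is not shown.
- *The bias favours the two-layer arm.* Higher pressure makes this plausible, but no exit rate by arm is given, and the tolerability studies cited in the Background compare two layers with four, not with crepe. The Background also says that light single-layer bandages do not control exudate and can cause overpressure, so more exits from the crepe arm are conceivable. The table shows that censoring can then understate the effect.
- *Any stopping of the bandage means leaving.* The first route covers only reactions severe enough to preclude continuing in the study, and the third is ordinary loss. Only the middle route directly equates not keeping the bandage with leaving.

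These points limit the claim. They do not answer the remaining one: a stated rule ends participation for a treatment-related reason, and no assessment afterwards is provided for.

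**Conclusion.** The point holds in limited form. The Withdrawal criteria and the intention-to-treat statement do not fit together: bandage-related exits leave week-12 healing uncollected, and the default handling in the planned analyses is censoring that is probably informative. The sign and size of the resulting bias cannot be determined from the article. The illustrated departures from the censored 20 points run from about 5.4 points too high (20% v 5% exits, k = 0.25) to about 2.3 points too low (5% v 20%, k = 0.25). They rest on assumed exit rates, exit times, constant hazards and healing after exit, and should be read as a range of possibilities, not a forecast. The contradiction itself needs no assumption, and it can be repaired only while outcomes can still be collected.

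**What to change.** Reconcile Withdrawal criteria with Analysis:

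1. Separate stopping the assigned bandage from leaving the study. Record stopping with its date and reason, and do not let it end participation.
2. Continue healing, Resvech and CCVUQ-e assessment to week 12 unless consent is withdrawn or the patient is lost under the existing Lost to follow up rule.
3. State that every randomised patient is analysed in the assigned arm, whatever bandage was worn.
4. For outcomes still missing, compare censoring with counting as not healed in a sensitivity analysis, since either can mislead.

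Nothing here alters when a bandage is stopped clinically.

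The cost is a change of protocol wording, one eCRF field, and continued assessments in patients who would otherwise have left. The estimated effect may be smaller, because it would include patients who could not wear the assigned bandage.

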### Analysis

Descriptive analysis of each variable with its corresponding 95 % confidence interval. Normality tests. Description of the profile of patients who withdraw from the study and their reasons for withdrawal.Comparison of the group at the beginning of the trial with regard to their descriptive and response variables and predictors. Bivariate statistical tests will be employed that are suitable for the variable type (qualitative or quantitative).Primary effectiveness analysis: A comparison will be performed of the incidence rates of ulcers with complete healing, using the ratio of incidence rates, with their point estimate and 95 % confidence interval. We will compare the time to complete healing using Kaplan-Meier curves for both types of treatment (log-rank test). To adjust for prognostic factors, we will perform a Cox regression model, with the time elapsed to complete healing as the dependent variable, complete healing as the event and the intervention group as the independent variable. We will include in the model those variables that can act as confounding factors or that can modify the effect.Secondary effectiveness analysis: For each secondary variable, we will apply the appropriate statistical technique based on the character of each variable (qualitative or quantitative) and to the distribution to which they fit (parametric or nonparametric).

The individuals responsible for performing the analysis will be unaware of which intervention each patient included in the study has undergone. All statistical analyses will be performed by intent-to-treat, using the conventional level of statistical significance (0.05).

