### Aim

The aim of this study is to assess whether multilayer compression bandages with 2 layers are more effective than crepe bandages in the healing of chronic venous ulcers in patients treated in primary care nursing consultations, measured by the incidence rate of ulcers with complete healing at 12 weeks of follow-up in each group.

The secondary objectives are to compare the effectiveness of the multilayer and crepe bandages (based on the degree of healing achieved and measured with Resvech 2.0), assess improvements in quality of life (measured with the Charing Cross Venous Ulcer Questionnaire [CCVuQ-e]) and analyse the sociodemographic, clinical and treatment factors associated with complete healing of venous ulcers.

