**Fig. 2 Fig2:**
[figure not shown]
Sequence of visits in Control and Experimental Group

The schedule of visits is shown in Table 1.

**Table 1 Tab1:** Schedule of visits

	Baseline visit Day 0	Visit 1 Day 1	Visit 2 Day 15	Visit 3 Day 30	Visit 4 Day 45	Visit 5 Day 60	Visit 6 Day 75	Visit 7 Day 90 End of follow-up
Verification of inclusion criteria	x							
Patient has signed the informed consent	x							
Randomisation	x							
Intervention		x	x	x	x	x	x	x
Resverch assessment		x	x	x	x	x	x	x
CCVUQ-e questionnaire		x						x
Collecting data on adverse reactions			x	x	x	x	x	x
Healing complete			x	x	x	x	x	x
Sociodemographic variables	x							
Prognostic variables		x						
Variables related to healing		x	x	x	x	x	x	x

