### Variables

#### Outcome variables

The main outcome variable is the Complete healing at 12 weeks of follow-up: (yes/no). *complete and sustained epithelialisation for at least 2 weeks. Time elapsed between start of the study and complete healing of the wound (in days).

Secondary outcome variables are: Degree of healing (Resvech 2.0); health-related quality of life for patients with venous ulcers (CCVUQ-e) and presence of adverse reactions.

The RESVECH 2.0 scale was used to monitor wounds [17]. Based on the results of a PhD thesis, it can be used to assess characteristics and evaluate the healing process in all types of chronic wounds. It assesses six parameters: wound size, depth of the affected tissues, status of the edges, type of tissue in the wound bed, level of exudate and inflammation-infection in the wound (presence of biofilm).

The CCVUQe is a specific tool to measure quality of life with venous ulceration [7], recently validated Spanish language version of the questionnaire.

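### RESVECH 2.0 and CCVUQ-e: the effect measure is left to the data, use of the Day 1 score is not committed to, and stopping data collection at healing conflicts with the Day 90 assessments

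*Protocol article*

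**What the plan says.** The article names three secondary outcomes: "Secondary outcome variables are: Degree of healing (Resvech 2.0); health-related quality of life for patients with venous ulcers (CCVUQ-e) and presence of adverse reactions". The point concerns the first two, which are scores.

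- **Choice of method (Analysis, secondary effectiveness).** The rule is "we will apply the appropriate statistical technique based on the character of each variable (qualitative or quantitative"), and also according "to the distribution to which they fit (parametric or nonparametric"). No test, outcome form (final score, change or repeated measures) or covariate is named. Adjustment for prognostic factors is stated only for the primary Cox model. Starting values of the response variables appear only in the comparison of the groups at entry.
- **Schedule (Table 1).** The row "Resverch assessment" is marked at every visit from Visit 1 (Day 1) to Visit 7 (Day 90). The row "CCVUQ-e questionnaire" has two marks, which read as Visit 1 and Visit 7.
- **Objective (Aim).** For CCVUQ-e the intention is to "assess improvements in quality of life".
- **End of follow-up (Data collection).** Collection runs for 12 weeks or "will finish early if the ulcer has healed".
- **Analysis set (Analysis).** All analyses are to be by intention to treat.

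**The concern.** There are two separate issues.

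**The selection rule.** If the distribution decides between a parametric and a nonparametric technique, the quantity estimated is fixed only after the data are seen. The rule also gives the starting score no stated role, although both scales are measured on Day 1. A comparison of final scores alone would give up precision that is already paid for and would leave chance imbalance at Day 1 in the estimate.

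**The stop at healing.** RESVECH and CCVUQ-e are both due at Day 90, but data collection ends when the ulcer heals. If that is followed literally, patients who heal before the last visit have no Day 90 value on either scale. For CCVUQ-e, Day 90 is the only follow-up measurement. Whether a value exists would then depend on the primary outcome, which is expected to differ between arms. Comparing the values that remain is not a comparison of the randomised groups, so this issue, unlike the first, can bring bias.

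**Working it through.** **1. The plan's own figure.** Inputs from Sample size: 58% healed with multilayer bandages, 20-point difference (so 38% in controls), alpha 0.05, power 80%, 10% loss. Sidedness is not stated; two-sided reproduces the figure. With pooled variance under the null and a mean proportion of 0.48:

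n = [1.960 × √(2 × 0.48 × 0.52) + 0.842 × √(0.58 × 0.42 + 0.38 × 0.62)]² / 0.20² = 96.8, so 97 per arm; 97 / 0.9 = 107.8, so 108.

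Both figures reproduce. They concern complete healing; the article gives no sample-size figure for either scale. I use 97 per arm below as the evaluable number.

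**2. What baseline adjustment is worth.** The baseline-final correlation r is not in the document, so r = 0.3 to 0.7 is an assumption. The true difference of 0.4 SD used for power is also an assumption. Relative to an unadjusted final score (variance 1), the variance is 1 − r² for ANCOVA and 2(1 − r) for a change score. The unadjusted standard error exceeds that of ANCOVA by the factor 1/√(1 − r²). For the final score alone, the smallest difference detectable with 80% power is (1.960 + 0.842) × √(2/97) = 0.402 SD, and power at 0.4 SD is 79.6%.

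| r | ANCOVA variance | SE, unadjusted / ANCOVA | Detectable difference, ANCOVA (SD) | Power, ANCOVA | Power, change score |
|---|---|---|---|---|---|
| 0.3 | 0.91 | 1.048 | 0.384 | 83.2% | 65.3% |
| 0.5 | 0.75 | 1.155 | 0.348 | 89.6% | 79.6% |
| 0.7 | 0.51 | 1.400 | 0.287 | 97.4% | 94.9% |

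At r = 0 ANCOVA and the final score have the same variance, so nothing is lost. ANCOVA is at least as precise as either alternative at every r shown.

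**3. Who has a Day 90 value if collection stops at healing.** At the planning rates:

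- multilayer: 97 × (1 − 0.58) = 40.7, about 41 unhealed;
- crepe: 97 × (1 − 0.38) = 60.1, about 60 unhealed.

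These counts take every healing as recorded before the last visit. A patient whose healing is first recorded at Visit 7 would still be scored there, so the numbers with a value would be somewhat higher. The article does not give the timing.

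**4. The passages side by side.** Table 1 expects both scales at Day 90 with no exception for healed patients. Data collection ends follow-up at healing. Analysis promises intention to treat. All three cannot hold for the Day 90 comparison unless healed patients are still assessed or a rule assigns them a value, and the article states neither.

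**The case against.** The strongest reply is that the article is condensed and the secondary-analysis sentence is generic. It names no test and excludes no covariate. A change score, ANCOVA or a mixed model would all satisfy it. The stated interest in improvement, with CCVUQ-e measured twice, suggests that the starting score will be used. The normality tests are listed with the descriptive analysis and the bivariate tests with the comparison at entry; neither is stated to be the secondary analysis. The model may stand in a full protocol or SAP that is not shown.

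Most of this stands. A reader might infer that the plan ignores the baseline scores and therefore loses precision. The document does not support that: it is silent on baseline and does not exclude it. The loss is conditional on the analysis chosen and on a correlation that is not given. If a change score were used, the gap in power to ANCOVA at r = 0.7 would be only 2.5 points (97.4% against 94.9%).

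A reader might also infer that healed ulcers are to be excluded from the RESVECH comparison. No passage says so. Healing and RESVECH are recorded at the same visits from Day 15, so a healed ulcer could have a score when healing is recorded, and an analysis of the last available score would keep it. For that reason I attach no power figure to an unhealed-only analysis, which the protocol does not propose.

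The reply does not remove two things. The article does state a selection rule, and that rule lets the distribution decide the effect measure. And the conflict between stopping at healing and the Day 90 schedule lies within the text itself; it is not a detail left to another document.

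**Conclusion.** The point holds in a limited form, for secondary outcomes only.

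- **Effect measure and baseline.** The rule leaves the effect measure to the data and does not commit to using the Day 1 scores. If final scores are compared unadjusted, the standard error is about 5%, 15% or 40% larger than with ANCOVA at assumed correlations of 0.3, 0.5 or 0.7, and no larger at zero. Under randomisation this is inefficiency, not bias.
- **Stop at healing.** Data collection, Table 1 and the intention-to-treat statement do not fit together. Followed as written, a Day 90 comparison of collected values would rest on about 41 v 60 of 97 per arm at the planning rates, selected by the primary outcome. This is the more serious part because it can bias the comparison. Whether it happens depends on how the stop rule is applied.

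The primary analysis and the sample size are unaffected.

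**What to change.** 1. For each scale, pre-specify a model for the final score with treatment group and Day 1 score as covariates. Report the adjusted mean difference with its 95% confidence interval.
2. Drop the distribution check as the selector of the method. Keep a rank-based analysis as a sensitivity analysis. This matters most for RESVECH, where at the planning rates 58% and 38% of patients would share the closed-wound score and a linear model may describe the data poorly.
3. State that healed ulcers keep the closed-wound RESVECH value in the Day 90 comparison.
4. Reconcile Data collection with Table 1, so that it is clear whether the Day 90 CCVUQ-e is obtained from patients who have healed. A carried-forward wound score cannot stand in for a quality-of-life questionnaire.

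The cost is small: analysis wording, plus clarification of an assessment already in the schedule. No additional patients or visits beyond those in Table 1 are needed.
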